## Abstract

**Introduction:**

Hepatocellular carcinoma (HCC) is the fastest-rising and fourth most common cause of cancer death worldwide. Liver cirrhosis is the largest underlying risk factor for HCC. Therefore, patients with cirrhosis should have regular ultrasound and biochemical screening to pick up early HCC. Early HCC can be cured; more advanced HCCs have limited treatment options and poor prognosis. Current screening methods are suboptimal with poor sensitivity in picking up early disease. In this study, the investigators aim to recruit people with liver cirrhosis into a Prospective cohort for early detection of liver cancer—the Pearl cohort. The investigators believe that by using state-of-the-art tests we can improve the detection of early HCC.

**Methods and analysis:**

This is a UK-based prospective, longitudinal, diagnostic, prognostic, multicentre, non-CTIMP study. Aiming to recruit 3000 patients with liver cirrhosis without a HCC diagnosis, the Pearl cohort will be followed actively for 3 years from recruitment and then passively via registry data for ten years thereafter. Blood and urine samples will be taken and information from routine care will be gathered. These will be used to assess novel diagnostic approaches for the detection early HCC and to develop models to identify those most at risk for developing HCC.

Participants will be linked to national UK health registries to ensure long-term capture of HCC incidence and other relevant endpoints. Approximately 75 patients are predicted to develop de novo HCC within the 3-year follow up period. After this period, the study teams will obtain data on participants for at least 10 years after the last contact. This cohort will help develop an understanding of the incidence of HCC in a UK population stratified by underlying cirrhosis aetiology.

**Ethics and dissemination:**

Ethical approval has been granted by REC and the trial is registered on ClinicalTrials.gov. The results will be published in peer-reviewed journals and presented at relevant meetings.

**Trial registration number:**

NCT05541601.

STRENGTHS AND LIMITATIONS OF THIS STUDYThe only large prospective cohort study to look at patients with cirrhosis across aetiologies while also exploring multiple state-of-the-art and established assays to help facilitate early diagnosis of hepatocellular carcinoma and develop models to help with risk stratification to enhance current screening programmes.The Pearl cohort aims to be representative of liver cirrhosis in the UK.Multiple academic and industry partners are invested in the study. Their expertise can be leveraged to develop new technologies.Data and samples will be collected over time via national UK health registries for long-term outcomes. Variable time of sample collection in relation to development of liver cancer.Comprehensive and real-time data capture and integration including the use of daily reporting, statistics, quality control and outlier detection.

## Introduction

Hepatocellular carcinoma (HCC) or primary liver cancer is a major global health problem. It is the fastest-rising and the fourth most common cause of death due to cancer worldwide,^1^ with 854 000 new cases and 810 000 deaths/year.^2^ In the UK, there are ~5500 HCC deaths/year as reported by Cancer Research UK (CRUK). From 1990 to 2015, HCC incidence has increased by 75% globally,^2^,^4^ particularly in high-income regions (including the USA and Europe). It is projected that by 2030, HCC will be the third-leading cause of cancer deaths, surpassing breast, colorectal and prostate cancers.^5^

HCC usually arises in patients with advanced liver fibrosis or cirrhosis: 90% of HCC develops on a background of liver cirrhosis^6 7^ (see figure 1); one-third of patients with liver cirrhosis develop HCC in their lifetime.^8^ In the UK, it is estimated that more than 60 000 people have cirrhosis.^9^ Liver cirrhosis can be caused by several different conditions, commonly: viral hepatitis B (HBV) and viral hepatitis C (HCV), alcohol excess, haemochromatosis or metabolic syndrome/obesity/diabetes. Worldwide 75% of HCC is associated with HCV or HBV cirrhosis. The recent advent of effective direct-acting antiviral therapies means that HCV-infected patients with cirrhosis are now cured of infection. However, HCC risk persists, and these patients are retained in surveillance programmes,^10^ with HCC annual incidence 1%–1.8%.^11 12^ The rise in rates of metabolic dysfunction-associated steatotic liver disease (MASLD) (previously known as non-alcoholic fatty liver disease) is increasingly contributing to the underlying HCC annual incidences (0.25%–7.6%).^13 14^ Genetic haemochromatosis contributes to HCC incidence, with UK Biobank data showing high clinical penetrance (>20% with genetic prevalence 1/156).^15^ Since people with liver cirrhosis represent a high-risk group for the development of HCC, these can be targeted for HCC screening for the early diagnosis of HCC (HCC-EDx).

**Figure 1 F1:**
[figure not shown]
Pathways to hepatocellular carcinoma (HCC)-targeting at-risk populations for surveillance. Alcohol, steatotic or fatty liver disease (FLD), haemochromatosis (Fe) and infection with hepatitis B or hepatitis C virus cause liver inflammation and fibrosis. If left untreated, this can progress to liver cirrhosis and one-third of all patients with cirrhosis will develop HCC. We will target this at-risk population for HCC early detection. Of note however, while 90% of HCC develops on a background of cirrhosis, transformation can occur independently of cirrhosis; in particular, up to 50% of patients with MASLD (NAFLD)-linked HCC will not have cirrhosis. MASLD, metabolic dysfunction-associated steatotic liver disease; NAFLD, non-alcoholic fatty liver disease.

The European Association for the Study of Liver Diseases recommends HCC surveillance in patients with cirrhosis with Child-Pugh A (CP-A), CP-B and CP-C awaiting liver transplant.^16^ Traditionally, HCC screening has relied on liver ultrasound, sometimes combined with alpha-fetoprotein (AFP) measurements. A 6-month interval for screening is standard; shorter intervals have no additional benefit,^17^ while longer intervals are associated with fewer early HCC diagnoses and shorter survival.^18^ Observational and randomised studies of HCC screening in cirrhosis indicate increased detection of HCC at an early stage, increased uptake of curative treatment and survival benefits with surveillance over symptomatic diagnosis, even after accounting for lead-time bias.^19 20^ However, current screening methods have low specificity and sensitivity.^21^,^23^ Indeed, with current surveillance strategies, up to 70% of UK patients have HCC detected at an advanced stage.^24^ Despite this, HCC screening using current existing suboptimal tools has been shown to be cost-effective when HCC incidence is >1.5%/year.^12 25^

Curative HCC therapies (eg, ablation/resection/transplantation) are only offered to patients with early disease (Barcelona Clinic Liver Cancer (BCLC) stages 0 and A). Beyond BCLC-A, the prognosis with all treatment options is poor; chemoembolisation is used for BCLC-B in patients with CP-A, with a mean survival of 2.5 years. Patients with CP-A cirrhosis and unresectable advanced HCC can be offered selective internal radiation therapy with an aim to down-stage the tumours or to bridge systemic medical therapies.^26^ Approved systemic therapies (sorafenib/lenvatinib) improve survival by only 2.3–2.8 months^27 28^ and are used in patients with BCLC-C disease with CP-A. Immune checkpoint inhibitors show antitumour effects in only 15%–20% of patients with HCC.^29^ Therefore, there is an urgent need to develop new strategies to detect HCC at the earliest possible time points when curative strategies may be offered to patients.

Although liver cirrhosis is the major risk factor for HCC, it is unclear why some people with cirrhosis develop HCC, while others do not. HCC is associated with a ‘field effect’ in the cirrhotic liver that predisposes to cancer transformation as evidenced by multiple HCC that arise contemporaneously. However, the pathways to malignant transformation remain unclear. Recent data suggest that malignant transformation in HCC is not primarily driven by archetypal cancer driver mutations.^30^ Furthermore, it is not known if there is a common biological pathway to HCC conversion, regardless of underlying disease aetiology.

Current biomarkers and imaging-driven technologies that aim to identify those most at risk for HCC and to detect HCC at the earliest possible time points are insensitive and outdated. They perform poorly for HCC-EDx and effective strategies for HCC-EDx are, therefore, urgently required. An EDx programme that improved risk stratification and HCC-EDx would significantly enhance the effectiveness of current surveillance programmes.

The Pearl study aims to create a large UK cohort of 3000 patients with liver cirrhosis, at risk for HCC that will be followed prospectively for 3 years, from multiple National Health Service (NHS) UK sites. The study cohort will be used to assess technologies to detect liver cancer at the earliest stages when curative therapies may be applied and to develop new models using a combination of clinical, molecular and genetic data to identify those most at risk for developing HCC. We hypothesise that the combination of state-of-the-art molecular diagnostics and clinical data can be used for the early detection and risk prediction of HCC.

The Pearl cohort will be part of a broader research programme ‘The early Detection of hepatocellular LIVER cancer (DeLIVER)’ which is funded by a 5-year programme grant from CRUK to the University of Oxford. SELiNa (The detection of Small Early Liver cancer with Natural history follow up study) is a sister study to Pearl within the DeLIVER programme, aiming to recruit 250 patients with small HCC. SELiNa is closely linked to Pearl and the data from both cohorts will be used to help evaluate the state-of-the-art assays being tested (see the ‘Objectives and outcome measures’ section).

## Methods and analysis

### Study design

Pearl will be a UK-based prospective, longitudinal, diagnostic and prognostic, multicentre study. This study is observational in nature and does not require any interventions (ie non-CTIMP (clinical trial of investigational medical product) or changes to standard clinical care.

The investigators aim to enrol 3000 participants from specialist liver clinics from multiple NHS hospital trusts in the UK. These trusts will be those that are part of the National Institute for Health Research Clinical Research Network (NIHR CRN) and NHS Research Scotland. Participants will have a diagnosis of liver cirrhosis and no history of HCC. All will be attending specialist services for management and treatment of their disease and routine screening for HCC. Enrolled participants will be asked to complete at least three visits; a baseline visit plus two further follow-up visits over a period of 3 years. An unscheduled visit may occur if a participant is diagnosed with HCC. During each study visit, participants will have samples taken and clinical data and information collected. Wherever possible, these study visits will be timed to coincide with routine clinic visits to minimise the burden for participants in terms of travel to the hospital, time spent in clinics, additional blood tests and other assessments.

Long-term follow-up of medical records from national health registries will be conducted for at least 10 years after the end of the active follow-up phase. Data obtained from NHS England and other patient registries will include decompensation episodes, HCC diagnosis, liver transplantation and death (see figure 2).

**Figure 2 F2:**
[figure not shown]
Pearl visit schedule highlighting prospective follow-up of participants. HCC, hepatocellular carcinoma.

### Recruitment

Participants for the Pearl study will be recruited at specialist clinics at NHS Hospital Trusts. Participants will be identified and screened to the inclusion and exclusion criteria by a member of the clinical care team or research team to ensure eligibility for the study. They will then be approached and given both written and verbal information regarding the study. Written informed consent will be obtained from every participant prior to enrolment at a clinic appointment. Eligible patients with cirrhosis may only attend clinic appointments every 6 months; therefore, it is anticipated that participants will be approached face-to-face about the study, consented and have their baseline visit on the same day. Patients who are eligible for the study but decline to participate will be logged into the site-specific study logs. This will allow for some level of review and analysis when looking at the final data set.

22 Pearl recruiting sites also participated in the MRC-funded STOP-HCV Cirrhosis Study and it is highly likely that surviving Cirrhosis Study participants will still be attending clinic and will be eligible to enrol into the Pearl study. STOP-HCV has a large dataset of deep-phenotyped participants with HCV-related cirrhosis successfully treated for HCV, followed prospectively since 2015 with annual blood sampling; we will ask permission of STOP-HCV Cirrhosis Study participants who are eligible and are recruited into Pearl to store their STOP-HCV study number for the purposes of data linkage.

### Participants

The investigators will recruit participants with Child- Pugh A or B cirrhosis with no current or historical diagnosis of HCC. Participants can be recruited to other interventional studies for treatment of cirrhosis or prevention of HCC prior to or during participation in the Pearl study.

### Inclusion criteria

Patients of all genders, age >18 years.Participants are willing and able to give informed consent for participation in the study.Evidence of cirrhosis Child-Pugh A or B (see table 1), with an underlying aetiology of at least one of the following:Chronic HBV infection.Chronic HCV infection.Alcoholic liver disease.MASLD.Haemochromatosis.

**Table 1 T1:** Cirrhosis diagnosis definition

Criteria A or one of criteria B		
Criteria A	Criteria B	
Histological Assessment(Ishak stage 5 or 6)	Validated non-invasive markers of fibrosis including FibroScan, APRI score >2 or ELF score >10.48 or Fibrotest score >0.73.	FibroScan readings should be assessed by aetiology: HBV: ≥10 kPa HCV: ≥14.5 kPa ALD: ≥19.5 kPa MASLD (NAFLD): ≥15 kPa Haemochromatosis: ≥12 kPa
	Evidence of varices at endoscopy or imaging in the context of a patent portal vein	
	Definitive radiological evidence of cirrhosis (ie, nodularity of liver and splenomegaly on ultrasound/CT)	

APRI score: AST to Platelet Ratio Index score

ELF score: Enhanced Liver Fibrosis score

ALDalcoholic liver diseaseHBVhepatitis B virusHCVhepatitis C virusMASLDmetabolic dysfunction-associated steatotic liver diseaseNAFLDnon-alcoholic fatty liver disease

### Exclusion criteria

Diagnosis of current or historical HCC.Liver transplant recipients or patients on active listing for liver transplantation.Child-Pugh C cirrhosis.In the view of the clinician, if the patient has a comorbidity likely to lead to death within the following 12 months.In the view of the clinician, if the patient is not thought to be suitable for HCC surveillance.

### Protocol procedures

Each participant will have three scheduled study visits: one baseline visit and two subsequent follow-up visits over a 3-year period. During the baseline visit, participants will be consented, enrolled into the study and allocated a unique study number. Their demographics, anthropological measurements (height, weight and body mass index), medical history and previous clinical imaging data will be collected. They will also have blood and urine samples collected and stored. All data and biological samples will be recorded against their unique study number.

During the two subsequent scheduled follow-up visits, 18 months after previous visits (which will be timed to coincide with routine clinic appointments where possible) there will be further collection of data as above (including blood and urine samples). If participants are unable to attend a face-to-face appointment the participant may be contacted via phone or email to respond verbally or online to a questionnaire (for medical history and demographic data).

Participants may have unscheduled follow-up visits. This will occur if the participant is diagnosed with HCC and should happen as close as possible to the date of HCC diagnosis. Participants will have the same data points, including blood and urine samples collected on this visit. Blood and urine samples will need to be collected prior to initiation of any treatment for HCC. Follow-up will then continue as per the standard protocol to ensure outcome data and samples are collected (see figure 2).

If the participant received a liver transplant, they would remain part of the study but no further follow-up visits or samples are required. If the participant dies the cause of death will be recorded clearly.

Beyond the 3-year active follow-up process, NHS England data from participants will be obtained for at least 10 years after the last participant contact. This passive follow-up will involve no direct participant contact.

### Sample handling and analysis

Participants will have blood and urine samples taken on each study visit (both scheduled and unscheduled). The research samples will be collected, have initial processing in the local laboratory and stored (as per sample collection protocol) prior to transfer to Oxford University labs.

Samples are handled and stored as per Human Tissue Act requirements; all samples are labelled with a unique visit ID and will not contain any personally identifiable information. All future subdivisions of the sample will be allocated a new unique barcode. Linking of clinical data to the samples will be possible using unique participant study numbers and visit ID numbers.

The blood samples will be tested for state-of-the-art biomarkers including (but not limited to):

Detection of epigenetic and genetic mutations and copy number variations in circulating tumour DNA.Polygenic risk scores derived from germline genetic sequencing.Detection of autoantibodies to tumour-associated antigens.Protein biomarkers include the L3 isoform of AFP and des-gamma-carboxyprothrombin.Viral sequencing (HBV and HCV).Proteomics and metabolomics.

The urine samples will be analysed for:

Proteomic and metabolomic profiling including steroid metabolic signatures in urine.

Analyses will be carried out in laboratories within the University of Oxford or with collaborators at other academic institutions. Participant consent for these analyses and storage and future use of remaining blood and urine samples for yet unspecified ethically approved research purposes will be sought. Samples will be retained indefinitely.

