### Objectives and outcome measures

The primary objective of Pearl is to determine the performance characteristics of novel state-of-the-art diagnostic approaches for the early diagnosis of HCC in study participants who are diagnosed with HCC by conventional means. For each novel diagnostic approach (whether as a single test or combination of tests) the outcome measures will be the sensitivity, specificity, and positive and negative predictive values in terms of HCC diagnosis for each test. The diagnostic approaches to be tested are as outlined in the section ‘Sample handling and analysis’. Evaluation of the outcome measures will begin once 50 cases of HCC have accumulated within the Pearl cohort.

The primary objective outlined above will be evaluated in conjunction with data from the DeLIVER sister study SELiNa. The Pearl cohort will be divided and used as part of the SeLiNa discovery cohort (providing non-HCC cirrhosis controls), and as the validation cohort (see figure 3).

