### Statistics and analysis

#### Primary objective (evaluate diagnostic performance of early diagnosis assays)

The investigators will assess the performance of selected detection assays for diagnosis of early HCC. This will be achieved by comparing assay values for early HCC cases with those of non-HCC controls (using the SELiNa cohort data). The performance characteristics of primary interest for each assay will be:

Sensitivity (ie, proportion of HCC cases with a ‘positive’ result).Specificity (ie, proportion of non-HCC cirrhosis cases with a ‘negative’ result).Positive predictive value (ie, probability of having HCC for individuals with a ‘positive’ result).Negative predictive value (ie, probability of not having HCC for individuals with a ‘negative’ result).

The area under the receive operating curve, derived from an assay’s sensitivity and specificity, will also be calculated as a summary measure.

As well as quantifying the performance characteristics of each assay in isolation, we will also assess the degree to which performance characteristics may be augmented by combining information from multiple assays into a single ‘multivariable’ model. Simplest methods will be considered first, considering increasingly complex methods if they provide value, for example, logistic regression, random forests, support vector machines.

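### Where a raised AFP prompts imaging, early HCC cases are partly selected on AFP, so the sensitivity of AFP-L3 is likely to be overstated

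*Protocol article*

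**What the plan says.** Under Sample handling and analysis, the protocol article lists the blood assays and includes an isoform of AFP: "Protein biomarkers include the L3 isoform of AFP and des-gamma-carboxyprothrombin". Objectives and outcome measures makes that list the set of index tests for the primary objective: "The diagnostic approaches to be tested are as outlined in the section" on sample handling. The same section fixes who counts as a case: performance is determined "in study participants who are diagnosed with HCC by conventional means". The article does not define conventional means further.

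Study design places every participant in ordinary surveillance: "All will be attending specialist services for management and treatment of their disease and routine screening for HCC". The Introduction, after Figure 1, says that "HCC screening has relied on liver ultrasound, sometimes combined with alpha-fetoprotein (AFP) measurements", and goes on to call the sensitivity and specificity of current screening low. The Abstract says that "patients with cirrhosis should have regular ultrasound and biochemical screening to pick up early HCC", without naming AFP.

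Statistics and analysis, under the primary objective, narrows the comparison to early disease: assay performance comes from "comparing assay values for early HCC cases with those of non-HCC controls". It adds that assays will be combined in multivariable models.

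**The concern.** AFP is a screening marker in the pathway that finds the cases, and AFP-L3 is a form of the same protein. Suppose a raised AFP leads to imaging in some participants. Early tumours that secrete AFP then have two routes to detection, while early tumours that do not secrete it have only ultrasound. An AFP-negative tumour missed on ultrasound may surface later at a more advanced stage, and is then no longer an early case. The early-HCC group becomes enriched for AFP-positive tumours, and an assay that tracks AFP looks more sensitive in that group than it is among all early tumours.

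A larger sample does not remove this. It can also favour AFP-derived markers when assays are measured on the same cases and combined in one model. The under-represented tumours are those that current surveillance misses, which is the gap the study sets out to close.

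**Working it through.** The article gives no figure for this point, so there is nothing to reproduce. I used a selection model to find the direction and plausible size of the effect.

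**Taken from the article:** AFP-L3 is an index test; cases come from conventional diagnosis within routine screening; AFP is used sometimes; screening sensitivity is low (no figure); evaluation starts at 50 HCC cases.

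**Assumed, because the article gives no values:**
- A, share of early HCC with raised AFP: 0.3 to 0.5
- U, ultrasound sensitivity for early HCC, taken as equal in AFP-positive and AFP-negative tumours: 0.45 to 0.80
- f, share of surveillance in which AFP is used and a raised value leads to detection: 0 to 1
- a and b, probability that AFP-L3 is positive in AFP-positive and AFP-negative HCC: 0.7 and 0.1
- m, share of initially missed tumours later recovered as early cases: 0, 0.5 or 1

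**Formulas:**
- True sensitivity = A·a + (1−A)·b
- Detection probability: d⁺ = f + (1−f)·U if AFP-positive, d⁻ = U if AFP-negative
- After recovery: D = d + (1−d)·m
- Observed sensitivity = [A·D⁺·a + (1−A)·D⁻·b] / [A·D⁺ + (1−A)·D⁻]

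**Worked case** with A = 0.4 and m = 0. True sensitivity = 0.4·0.7 + 0.6·0.1 = 34.0%. With U = 0.60 and f = 1, d⁺ = 1 and d⁻ = 0.60, so observed = (0.28 + 0.036) / (0.40 + 0.36) = 0.316/0.76 = 41.6%.

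| U | f | Observed (true 34.0%) | Excess, points |
|---|---|---|---|
| 0.60 | 0 | 34.0% | 0 |
| 0.60 | 0.3 | 36.7% | 2.7 |
| 0.60 | 0.5 | 38.2% | 4.2 |
| 0.60 | 1 | 41.6% | 7.6 |
| 0.45 | 1 | 45.8% | 11.8 |
| 0.80 | 0.3 | 35.0% | 1.0 |

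Over A = 0.3 to 0.5, U = 0.45 to 0.80 and f = 0.3 to 1, the excess is about 1 to 12 points when m = 0. It is about 0.4 to 5 points when m = 0.5. It is zero when m = 1, when f = 0, or when a = b.

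**Scale.** At 50 cases the 95% half-width is 1.96·√(0.34·0.66/50) = 13.1 points at a sensitivity of 34%, and 13.6 points at 40%. The bias would therefore usually be smaller than the sampling error at the first evaluation, but only the sampling error shrinks as cases accrue.

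**Which subset is free of the selection?** Among cases that ultrasound found, whatever their AFP, sensitivity = [A·U·a + (1−A)·U·b]/U = A·a + (1−A)·b = 34.0%, the true value. By contrast, if f = 1 and every case with a raised AFP counts as AFP-prompted, the remaining cases are all AFP-negative and show b = 10%, far below the truth. The ultrasound-found subset is therefore the right comparison, and the subset not prompted by AFP is at best a lower bound.

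**The case against.** The strongest reply is that the links are not all in the text. AFP is described as used sometimes, in a general account of screening; the article does not report AFP use at the Pearl sites, that a raised value prompts imaging there, or that AFP-L3 follows total AFP. That stands. A reader might infer that overstatement is certain, but the documents support only a conditional statement, and the model gives zero where a condition fails.

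A reader might also infer that AFP is built into the reference standard. The text does not show this. It describes how HCC is screened for, and nothing says that AFP contributes to confirming the diagnosis. Nor does every panel containing AFP-L3 inherit the problem in full: one driven by other markers would be affected less.

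It is tempting to measure the bias as the gap between all cases and cases not prompted by AFP. If AFP-L3 were positive in 80% of AFP-prompted and 30% of other early cases, with 10%, 25% or 40% prompted, the all-case figure would be 35%, 42.5% or 50%, a gap of 5 to 20 points. That gap is not the bias, because the comparison group has been selected against AFP-positive tumours. The same gap would appear even if ultrasound would have found every one of those tumours anyway.

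A further reply is that missed tumours come back. Every participant diagnosed with HCC during active follow-up has an unscheduled visit, and registries are followed for at least 10 years. This helps only in part. A missed tumour found at a later screening round while still early does return, which is why m is varied above. One found at an advanced stage does not return to the early group, and passive registry follow-up involves no participant contact and so yields no sample at diagnosis.

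Finally, a detection-route field and a stratified table may already be in the case report form or analysis plan. Their absence from a condensed article is not the fault raised here. The point arises from what the article does state: the index test, the source of cases and the restriction to early disease.

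**Conclusion.** The concern holds in conditional form. Where AFP is part of surveillance and a raised value prompts imaging, the early-HCC group is partly selected on AFP, and AFP-L3 sensitivity is likely to be overstated. A panel is affected to the extent that its result follows AFP-L3. Three conditions are needed: AFP prompts some work-ups, ultrasound alone misses some early tumours, and AFP-L3 is more often positive when AFP is raised.

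The size cannot be derived from the documents. The range of about 1 to 12 points rests entirely on assumed inputs with no recovery of missed tumours, and shrinks as more of them are recovered as early cases. No passage is in error. This is a design weakness that is cheap to address, and easiest to address prospectively, before the evaluation at 50 cases.

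**What to change.** At the HCC visit, record from the medical notes the surveillance ultrasound result, the AFP result and what prompted diagnostic imaging. No change to care, visits or samples is involved.

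For AFP-L3 and each panel containing it, report two sensitivities side by side: in all early cases, and in early cases that surveillance ultrasound found, whatever their AFP. The second group is not selected on AFP, provided that ultrasound visibility is itself unrelated to AFP status; state that assumption with the result. An ultrasound repeated because AFP was raised should not count as a surveillance finding.

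A figure restricted to cases not prompted by AFP may be added, labelled as a lower bound. It should not be used to rank assays or select markers, because it is biased against AFP-L3. Apply the same split to SELiNa cases if their detection route is available; the article does not describe it.

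The cost is a short record entry, one extra table and a wider interval. In the worked case with f = 1 and U = 0.60, ultrasound found 0.60/0.76 = 79% of detected cases. If all 50 were early, that is about 39, and the half-width at 34% rises from 13.1 to 1.96·√(0.34·0.66/39) = 14.9 points.
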